**Methods/Design:**

The study is a randomized controlled pilot clinical trial of five weeks duration. Fourteen patients will be recruited and randomly allocated to two groups: an acupuncture plus interlaminar epidural steroid injection group (experimental group), and an interlaminar epidural steroid injection group (control group). All patients will be administered an interlaminar epidural steroid injection once a week for three weeks (three injections in total), but only the experimental group will receive additional treatment with three acupuncture sessions a week for three weeks (nine acupuncture sessions in total). The primary outcome will be measured by the visual analogue scale (VAS). Our primary end point is three-week VAS. The secondary outcome will be measured using the PainVision system, the short-form McGill Pain Questionnaire, and the Oswestry Disability Index. Assessments will be made at baseline and at one, three and five weeks thereafter (that is, the five-week assessment will be made two weeks after treatment cessation).

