## Methods/Design

### Design

The study is a randomized controlled pilot clinical trial. It is designed to assess the efficacy and safety of acupuncture treatment in patients with low back pain due to low-grade spondylolisthesis. The protocols used adhere to the principles of the Declaration of Helsinki and have been approved by the institutional review board of Daegu Catholic University Hospital (IORG0004453), where the study will take place. The trial is registered with the US National Institutes of Health Clinical Trials registry. Written consent will be obtained from each participant before any treatment is given.

The outcome assessment and statistical analyses will be performed by professionals blinded to the assignment of patients. The trial process is presented in Figure 
1. The trial will run for five weeks. Patients will be allocated to two groups; the control group will only receive three interlaminar epidural steroid injections and the experimental group will receive all three steroid injections as well as nine acupuncture sessions (three sessions a week forthree weeks). Assessments will be made at baseline, and again at one, three and five weeks thereafter. The week five assessment will be performed two weeks after treatment cessation.

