### Participants

One of the main objectives of this study is to provide an estimate of the sample size required for the full-scale randomized controlled clinical trial. We plan to recruit 14 patients into this pilot study. A target of 14 patients with spondylolisthesis has been set.

The inclusion criteria are that participants must: be aged 18 to 65 years, have Meyerding Grade I to II spondylolisthesis, have low back pain of at least one-year duration, be available for possible follow-up during the clinical trial, and provide written informed consent voluntarily.

The exclusion criteria are: cauda equina syndrome, persistently exacerbated symptoms, progressive neurologic signs (sensory or motor changes); previous spine surgery; senile dementia, impaired cognitive function or other cerebral disease, severe psychiatric or psychological disorders; severe, concomitant disease (neuromuscular scoliosis, neurodegenerative disease); all contraindications to corticosteroid injection (e.g., insulin-dependent diabetes); alcohol/drug abuse; significant renal or hepatic disease; pregnant, lactating or planning a pregnancy; hypersensitive reaction to acupuncture treatment; inability to comprehend or express oneself in the Korean language; an individual deemed to be ineligible by a physician; or refusal to participate in the trial or to provide informed consent.

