### Randomization

Patients will be randomized using a computerized random number generator by an independent statistician blinded to patient assignment. Block randomization will be performed once a participant is confirmed to be eligible and their written informed consent has been obtained.

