### Safety

We will confirm the safety of acupuncture by determining the red blood cell (RBC) count, hemoglobin level, platelet count, mean corpuscular volume (MCV), mean corpuscular hemoglobin (MCH), mean corpuscular hemoglobin concentration (MCHC), hematocrit (Hct), total white blood cell (WBC) count, erythrocyte sedimentation rate (ESR), aspartate aminotransferase (AST), alanine aminotransferase (ALT), serum urea nitrogen (BUN), creatinine level, serum sodium level, serum potassium level, and serum chloride level. All patients were evaluated two times, including the screening visit and after the termination of acupuncture.

Any reported adverse events will be recorded throughout the study and vital signs will be monitored at each visit. The patients will be requested to voluntarily report information about adverse events, and the researcher will confirm the occurrence of adverse events through methods such as a medical interview. Details about adverse events, such as the date of occurrence, degree of adverse events, causal relationship with the treatment, other treatments or medications that are suspected to cause the adverse event, and treatment of the adverse event, will be recorded in detail.

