### Statistical analysis

The statistical significance level will be set at 5%, and the data will be analyzed using intention-to-treat and per protocol approaches. Data will be processed with the last observation carried forward method for the intention-to-treat analysis, and will be performed using IBM SPSS Win ver. 19.0 statistical software (IBM Co., Armonk, NY, USA).

All demographic and clinical characteristics of the subjects (such as sex, age, and weight) will be processed based on descriptive analyses. Quantitative data will be presented as average, standard deviation, median value, and range. Qualitative data will be presented as the frequency and percentage. The study will identify the comparative equivalence of demographic variables and clinical characteristics between the experimental and control groups.

In order to identify differences in VAS, PainVision scores, SF-MPQ and ODI scores between the experimental and control group based on time (baseline, weeks one, three and five), a repeated-measure twofactor analysis will be performed to identify differences between groups, differences within each group based on time, and the effects of the interaction of the variables based on group. If the interaction between group and time is statistically significant, the point at which the pattern of results between the two groups changes will be checked.

The Chi-square test will be used to compare groups and the incidence frequency of adverse events related to acupuncture and interlaminar epidural steroid injection.

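### The planned chi-square test of adverse events is unreliable for every table 14 patients can give, and acupuncture-related events are zero by design in the control arm

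*Protocol article*

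**What the plan says.** The Statistical analysis section of the protocol article fixes one test for adverse events: "The Chi-square test will be used to compare groups and the incidence frequency of adverse events related to acupuncture and interlaminar epidural steroid injection." It names no exact or small-sample method for this comparison, and it sets the significance level at 5%. It does not say whether the two kinds of event are pooled or tested separately.

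The size of the trial is in the Participants section: "We plan to recruit 14 patients into this pilot study." The Abstract adds that these are allocated to two groups. The allocation ratio is not given; the Randomization section says only that "Block randomization will be performed once a participant is confirmed to be eligible" and consent has been obtained.

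On exposure, the Design section says that "the control group will only receive three interlaminar epidural steroid injections", while the experimental group receives the same injections plus nine acupuncture sessions. No sham acupuncture is described.

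On collection, the Safety section says that "The patients will be requested to voluntarily report information about adverse events". It also says that reported events are recorded throughout the study, that the researcher confirms them by means such as an interview, and that the causal relationship with treatment is recorded for each event. Safety of acupuncture is part of the primary aim stated at the end of the Background.

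**The concern.** Two features of the stated analysis do not fit the trial.

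First, the chi-square test rests on a large-sample approximation, usually trusted only when expected cell counts are about 5 or more. Fourteen patients in a two-by-two table cannot reach that.

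Second, part of the comparison concerns events that only one arm can have. A patient who gets no needles cannot have a needle-related event, so the control count is known before the trial starts.

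Because safety is part of the primary aim, the resulting p-value may well be quoted. A p-value below 0.05 could be a product of the approximation. One above 0.05 is the likely result whatever the truth, and could be taken as reassurance.

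**Working it through.** **Inputs.** From the protocol: N = 14, two groups, 5% level, no acupuncture in the control arm. Assumed: a 7:7 split (6:8 tried as well), two-sided testing, and the chi-square without continuity correction, since the plan does not say which form. The protocol gives no adverse-event rate or power, so there is no figure of the plan's own to reproduce; the rates below are assumptions.

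**1. Expected counts.** The smallest expected count is (smaller arm × smaller outcome total) / 14.

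- Neither factor can exceed 7, so the maximum is 7 × 7 / 14 = 3.5, for any split.
- At 6:8 the maximum is 6 × 7 / 14 = 3.0.
- At 7:7 at least two of the four cells are always below 5. All four are below 5 when 5 to 9 patients have an event.

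**2. Does the choice of test matter at 5%?** For 4/7 v 0/7:

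- Chi-square = 14 × (4×7 − 3×0)² / (7 × 7 × 4 × 10) = 10976 / 1960 = 5.60, p = 0.018.
- Fisher = 2 × C(7,4) / C(14,4) = 2 × 35 / 1001 = 0.070.

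For 5/7 v 1/7:

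- Chi-square = 14 × (5×6 − 2×1)² / (7 × 7 × 6 × 8) = 10976 / 2352 = 4.67, p = 0.031.
- Fisher = 2 × (21×7 + 7×1) / 3003 = 308 / 3003 = 0.103.

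| Table (experimental v control) | Chi-square | Continuity-corrected | Fisher |
|---|---|---|---|
| 4/7 v 0/7 | 0.018 | 0.076 | 0.070 |
| 5/7 v 1/7 | 0.031 | 0.105 | 0.103 |
| 3/6 v 0/8 | 0.024 | 0.110 | 0.055 |
| 4/6 v 1/8 | 0.036 | 0.126 | 0.091 |

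The last two rows show that the disagreement does not depend on a 7:7 split.

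**3. Overall type I error of the uncorrected test**, summing binomial probabilities over all tables with p ≤ 0.05, with the same event rate in both arms:

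| True rate | 7:7 | 6:8 |
|---|---|---|
| 5% | 0.03% | 0.2% |
| 10% | 0.3% | 1.0% |
| 20% | 1.8% | 3.8% |
| Maximum over all rates | 5.7% | 6.6% |

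The test is far below its nominal level when events are uncommon and only slightly above it at worst.

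**4. The structural zero.** With the control count fixed at 0 of 7, the p-value depends only on the number of acupuncture patients with an event:

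| Experimental arm | Chi-square | Fisher |
|---|---|---|
| 3/7 | 0.051 | 0.192 |
| 4/7 | 0.018 | 0.070 |
| 5/7 | 0.005 | 0.021 |

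The test thus reduces to asking whether at least 4 of 7 patients (chi-square) or 5 of 7 (Fisher) had an event. If the true rate is 30%, the chance of this is P(X ≥ 4) = 0.0972 + 0.0250 + 0.0036 + 0.0002 = 12.6% by chi-square, and P(X ≥ 5) = 2.9% by Fisher.

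**5. What the acupuncture arm can show by itself.** With 0 events in 7 patients the exact two-sided 95% upper limit is 1 − 0.025^(1/7) = 0.410, or 41%.

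**6. A comparison both arms can enter.** For assumed rates of 30% v 10%, chi-square power at 7:7 is 7.2%, and about 62 patients per arm would be needed for 80%.

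**The case against.** The strongest reply is that the test does little harm. Its overall false-positive rate never exceeds 5.7% at 7:7 and is close to zero at low event rates. A reader might instead cite 10.3% (308/3003), the false-positive rate when exactly 6 or 8 of the 14 patients have an event. That is the worst conditional case: at 7:7 the rate is 0% with three or fewer such patients, 7.0% with four, 2.1% with five and 2.9% with seven. So a claim of large type I inflation is not supported. What stands is that individual p-values near 0.05 cannot be relied on.

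A second reply is that the sentence also covers injection-related events. Both arms receive the injections, and asking whether adding acupuncture raises the total event burden is a fair question for an add-on design. This stands. It would be wrong to call the whole comparison empty; only the acupuncture-related part is.

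A third concerns collection. From Table 1, with about nine treatment visits in one arm and three in the other, a reader might infer that events are gathered at those unequal visits. The protocol does not say so. It records events throughout the study, has the researcher confirm them, and gives both arms the same assessments at weeks 1, 3 and 5. More contact may raise voluntary reporting in the acupuncture arm, but that is a possible bias whose size the document does not allow one to estimate.

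A fourth is that the statement "We will confirm the safety of acupuncture by determining the red blood cell (RBC) count" shows overclaiming. That sentence introduces the laboratory panel, not this comparison, and the present point does not rest on it.

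Finally, Fisher's test is even less likely to reject than chi-square. This is true, and is why the intervals rather than a p-value should carry the conclusion.

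**Conclusion.** The point holds in a limited form. The expected-count argument needs only N = 14 and two groups. The structural zero needs only that control patients get no acupuncture. The particular p-values rest on an assumed split and the uncorrected statistic; with the continuity correction the tabulated results agree with Fisher's test about significance at 5%. The consequence is an unreliable and nearly uninformative p-value on part of the primary aim, not a seriously inflated error rate and not a documented bias in collection. It should be corrected, but it does not endanger the pilot.

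**What to change.** Replace the chi-square sentence with the following:

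- Report, per arm, the number of patients with any adverse event and the number with an injection-related event, each with an exact 95% confidence interval. If a p-value is wanted, use Fisher's exact test.
- Report acupuncture-related events in the acupuncture arm only, with an exact interval and no between-group test.
- State that a non-significant difference will not be read as evidence of safety.
- When interpreting the all-cause comparison, note that the acupuncture arm has more treatment contacts, which may raise voluntary reporting.

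The cost is a few sentences. Causal relationship is already recorded for each event, so no new data are needed and nothing changes for patients in a trial that is already recruiting. The change should be dated before the safety data are analysed. The one drawback is Fisher's lower power (2.9% against 12.6% at assumed rates of 30% v 0%), which matters little if the intervals carry the conclusion.

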## Discussion

Recently, there has been increased interest in the use of acupuncture for treating diseases
[28]. Many studies have reported that acupuncture is suitable for providing pain relief and improving function in patients with low back pain
[29]. However, there is currently no evidence supporting the use of acupuncture in patients with low back pain due to low-grade spondylolisthesis. Our pilot study will evaluate the feasibility of further research on acupuncture as an effective and safe treatment for reducing pain and improving function in these patients. Although many surgical options exist for the treatment of spondylolisthesis, it is generally agreed that in most cases, conservative treatment should be attempted before surgical intervention.

Many clinical trials have compared surgical treatment methods. However, no randomized clinical trial has established an optimal non-operative treatment protocol
[4]. Our study is related to low-grade spondylolisthesis to apply conservative treatment at first. This randomized controlled pilot trial will inform the design of a further full-scale trial. The outcomes will provide some resources for incorporating acupuncture into existing pain management programs such as interlaminar epidural steroid injection for treating low-grade spondylolisthesis.

### Trial status

This trial is currently recruiting participants. Enrollment and trial completion is expected to be finished by the end of 2013.

## Abbreviations

ALT: alanine aminotransferase; AST: aspartate aminotransferase; BUN: serum urea nitrogen; ESR: erythrocyte sedimentation rate; Hct: hematocrit; MCH: mean corpuscular hemoglobin; MCHC: mean corpuscular hemoglobin concentration; MCV: mean corpuscular volume; ODI: Oswestry Disability Index; PPI: Present Pain Intensity; RBC: red blood cell; SF-MPQ: Short form McGill pain questionnaire; VAS: Visual analogue scale; WBC: white blood cell.
